#### Longer term clinical outcomes

Numbers of events and numbers (%) of patients with events will be summarised. Time to first event of each type will be analysed using Cox proportional hazards regression models, with estimated hazard ratios, 95% CIs and p values using the Wald statistic. Time to event curves will be created using the Kaplan-Meier method.

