**Figure 1 OPENHRT2015000371F1:**
[figure not shown]
Flow diagram of Coronary Artery Bypass Graft-Acute Coronary Syndrome (CABG-ACS) trial. Patients who provide consent will enter either the (1) randomised trial or (2) registry (ie, based on the presence of exclusion criteria, or physician or patient preference). Patients who do not provide consent and/or are ineligible will enter the (3) screen failure group. A change in the treatment strategy (eg, from non-invasive to invasive management, or vice versa) within the first 30 days from randomisation is a cross-over.

*Primary aims*: (1) Compared with routine non-invasive management, to assess if a routine invasive strategy is more effective in symptomatic patients with prior CABG compared with OMT; (2) compared with routine invasive management, to assess if a routine non-invasive strategy is associated with fewer major complications and hence is safer; (3) to prospectively quantify resource utilisation in the NHS with each treatment strategy, derive the difference in the quality-adjusted life years (QALYs) and hence provide preliminary health economic information.

*Secondary aims*: To evaluate: (1) the components of the primary composite outcomes for efficacy and safety; (2) quality of life (EuroQol 5 Dimensions (EQ-5D) at baseline and six monthly intervals for a minimum of 18 months); (3) Canadian Cardiovascular Society (CCS) angina class at baseline and six monthly intervals for a minimum of 18 months; (4) repeat invasive management during follow-up; (5) freedom from coronary and/or bypass graft intervention; (6) secondary care costs; (7) the nature and extent of multimorbidity during the index hospitalisation; (8) the nature and extent of native coronary artery and graft disease, including culprit lesion characteristics; (9) a registry of the patients who were not randomised, including the reasons for not being randomised (physician-directed, patient-directed or both) and their clinical characteristics at enrolment and subsequent outcomes during follow-up.

Accordingly, all invasive coronary interventional procedures will be reported:
Elective;Non-elective unplanned (as adjudicated by the CEC).

*Health economics*: Quality of life, direct healthcare costs, adverse events and their economic consequences over a patient's lifetime are key considerations to inform whether or not a routine conservative approach would be acceptable in patients with NSTE-ACS with prior CABG.^12^

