*Registry*: Information will be prospectively recorded in a registry for patients with an acute NSTE-ACS and prior CABG who are not randomised. The reasons for non-participation in the randomised trial will be prospectively recorded. The reasons may be the presence of exclusion criteria, unsuitability for either invasive or non-invasive management, physician preference, patient preference, or a combination of these factors. The registry information will provide insights to reflect an ‘all-comers’ real-world population. The registry will also inform on the feasibility of a future substantive randomised trial. The baseline information and the follow-up assessments are intended to be collected in the same way for the registry and randomised trial participants. Information (clinical characteristics, invasive and non-invasive tests, health outcomes and quality of life during follow-up) in the registry patients will be obtained in the same way as the trial patients, that is, with case note review, telephone contact or a hospital visit and during the longer term by electronic record linkage.

*Screen failure*: For screened patients who are (1) eligible but do not consent to participate in the randomised trial or registry, or (2) ineligible, then the reason(s) for not participating will be documented. No further clinical information will be recorded.

*Sample size calculation*: The sample size in the CABG-ACS pilot trial is n=60 patients. We chose this number in order to gain reasonably representative information on the characteristics of patients with NSTE-ACS with prior CABG in contemporary practice to be enrolled in different secondary care settings in order to be representative of the diversity in UK hospitals. We included four hospitals differing in geographic location, availability of catheter laboratory facilities onsite (or not), and hospital type (academic vs regional).

The sample size was selected to enable the feasibility of randomisation, and the reasons for not being randomised were to be prospectively assessed on multiple occasions. As this pilot was an exploratory, proof-of-concept trial, a sample size calculation was not performed. The trial was designed but not powered to assess for between-group differences in the rates of the primary outcome.

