### Clinical Event Committee

An independent CEC is proposed to review the primary efficacy and safety end points. The CEC will review cases of interest to determine if they meet the criteria defined in this charter. Causality assessments will not be made by the CEC, nor will the committee possess governance authority. The CEC will be blinded where possible regarding all information relating to the randomisation group. The CEC will include four cardiovascular physicians who have expertise in the diagnosis and treatment of cardiovascular disorders and in the medical aspects of clinical trials. The CEC will have a Chairman and coordinator to assist with preparation of de-identified source clinical data, reports and communication with the Trials Unit. The CEC will follow a predetermined adjudication charter.

*Primary outcome*: The primary outcome is the postrandomisation rate of major adverse events (co-primary composite outcome), including one composite outcome for *efficacy* and one composite outcome for *safety*. The comparison between the incidences of each outcome according to treatment group will assess the between-group difference in the proportion of major adverse events in patients allocated to non-invasive conservative management compared with invasive management. The trial is designed to assess the feasibility of recruiting and randomising such a population but is not powered to detect a between-group difference in clinical outcomes.

*Primary efficacy outcome*: Defined as all-cause mortality, rehospitalisation for refractory ischaemia/angina, MI or hospitalisation for HF. The end points will be assessed during the study until the final randomised patient has completed 18 months follow-up.

*Primary safety outcome*: Defined as bleeding (Bleeding Academic Research Consortium (BARC) types 2–4),^36^ stroke, procedure-related MI (type 4a, universal definition), worsening renal function or haemodialysis during the index hospitalisation.

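### The Wald intervals and p values fixed for every longer-term event type become unusable when one arm of about 30 patients has no events of that type

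*Protocol article*

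**What the plan says.** The article's section on longer term clinical outcomes summarises event counts and the numbers and percentages of patients affected. It then models time to first event, type by type, by Cox regression "with estimated hazard ratios, 95% CIs and p values using the Wald statistic". It adds: "Time to event curves will be created using the Kaplan-Meier method". No alternative is given for an event type with an empty arm.

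Single event types will be analysed, because the first secondary aim is to evaluate "the components of the primary composite outcomes for efficacy and safety". The efficacy composite is "Defined as all-cause mortality, rehospitalisation for refractory ischaemia/angina, MI or hospitalisation for HF", and on follow-up the article says: "The end points will be assessed during the study until the final randomised patient has completed 18 months follow-up".

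On size: "The sample size in the CABG-ACS pilot trial is n=60 patients". Table 2 splits them 31 invasive and 29 conservative. The article says that "a sample size calculation was not performed" and that the trial "is not powered to detect a between-group difference in clinical outcomes".

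The next section, on shorter term safety outcomes, uses Fisher's exact test and exact logistic regression.

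**The concern.** Wald inference for a Cox model needs a finite maximum of the partial likelihood and a roughly quadratic likelihood around it. With no events in one arm there is no finite maximum. The printed hazard ratio and standard error then depend on the software's stopping rule, and the p value drifts towards 1 even when the other arm has several events. The article provides for sparse data in the short-term outcomes but fixes a method that cannot cope with it for the longer-term ones.

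The pilot's purpose is to supply inputs: the article wants its data to feed an economic model and to guide the outcomes and size of a later trial. An interval of zero to infinity and a p value near 1 say nothing usable about a component on which the data do carry some information.

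A lesser issue concerns the curves. For a non-fatal event, one minus Kaplan-Meier with deaths censored estimates risk as if nobody died, and so overstates the share of patients who will have the event.

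**Working it through.** **Inputs.** Arms of 31 and 29 (Table 2; 31 + 29 = 60). The article gives no component risks or mortality, so those below are assumptions, shown over a range. It has no power or event target to reproduce.

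**1. How often is exactly one arm empty?** With a common risk p, the probability is (1−p)^31 + (1−p)^29 − 2(1−p)^60.

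| Risk p | Exactly one arm empty |
|---|---|
| 2% | 0.535 + 0.557 − 2 × 0.298 = 0.50 |
| 3% | 0.48 |
| 5% | 0.204 + 0.226 − 2 × 0.046 = 0.34 |
| 7% | 0.20 |
| 8% | 0.15 |
| 10% | 0.038 + 0.047 − 2 × 0.002 = 0.08 |
| 15% | 0.015 |
| 20% | 0.003 |

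With unequal risks of 3% v 10% and 5% v 15% it is 0.40 and 0.21.

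**2. What does Wald report then?** Take 4/31 v 0/29 with no censoring before the last event. The risk sets are 31, 30, 29 and 28 in the arm with events and 29 throughout in the other.

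- *Wald.* For large β the information is close to 29·e^(−β)·(1/31 + 1/30 + 1/29 + 1/28) = 3.94·e^(−β), so SE ≈ e^(β/2)/1.984. At β = 10, 15 and 20 the SE is 75, 911 and 11,100, and p is 0.89, 0.987 and 0.999. The ratio β/SE goes to zero as β grows.
- *Log-rank.* Expected events in the arm of 31 are 31/60 + 30/59 + 29/58 + 28/57 = 2.016. O − E = 1.984, V = 1.000, χ² = 3.94, p = 0.047.
- *Unpenalised likelihood ratio.* 2[ln(60·59·58·57) − ln(31·30·29·28)] = 2(16.275 − 13.535) = 5.48, p = 0.019. The profile-likelihood 95% interval has a lower limit of 1.60 and no finite upper limit.
- *Firth.* Adding ½·ln(information) to the log partial likelihood gives β = 2.18, HR 8.9, 95% CI 0.95 to about 1,174 and penalised likelihood-ratio p = 0.057.
- *Fisher's exact test on the counts.* p = 0.113.

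**3. Does Wald respond to the data at all?** For 0/31 v 3, 4, 5, 6 and 8 events among 29, with the iteration stopped at β = −20, the Wald p is 0.998 to 0.999 every time. The log-rank p falls through 0.068, 0.034, 0.017, 0.008 and 0.002.

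**4. Size of the Kaplan-Meier effect, if deaths are censored.** With constant hazards h = −ln(1 − risk), cumulative incidence is h_e/(h_e + h_d) × [1 − e^−(h_e + h_d)].

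- Event 20%, death 20%: 0.5 × (1 − 0.80 × 0.80) = 18.0%, against 20% from one minus Kaplan-Meier.
- Event 20%, death 10%: 19.0% against 20%.
- Event 5%, death 10%: 0.0513/0.1566 × (1 − 0.95 × 0.90) = 4.7% against 5.0%.

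**The case against.** The strongest reply is that little turns on this. The trial is an unpowered pilot with no decision rule tied to a component p value. Counts and percentages are reported anyway, the general statistics paragraph adds a χ² test of proportions, and any statistician would recognise an infinite hazard ratio as not estimable. That limits the harm and stands as far as it goes. It does not repair the hazard ratio, interval and p value that the article also promises.

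Some stronger readings are tempting but unsupported:

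- *That Wald hides a clear treatment difference at 4 v 0.* The p of 0.019 comes from the unpenalised likelihood ratio. Firth gives 0.057 and Fisher 0.113, so the data are suggestive at most. Wald's fault is that it conveys nothing, not that it misses a proven effect.
- *That the primary results are compromised.* An empty arm for the composite has a 1.5% chance at 15% risk. The primary safety outcome is confined to the index admission, where exact methods are specified.
- *That many components will certainly be affected.* No event rates are given, so the frequency is conditional on assumed risks.
- *That Kaplan-Meier also fails with an empty arm.* It does not. It is also sound for all-cause death and for the composite, which includes death.
- *That the curves are materially biased.* The article does not state that deaths are censored or that a curve is drawn for each event type. Even at 20% risk and 20% mortality the gap is 2 points, against a standard error of √(0.2 × 0.8/30) = 7.3 points in an arm of 30.

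**Conclusion.** The concern holds for rare single components of the longer-term outcomes. At assumed risks of 2% to 10% per arm there is a 50% to 8% chance that exactly one arm is empty, and the specified Wald interval and p value are then meaningless. The divergence is a property of the method and rests on no assumption; only its frequency depends on the assumed risks. The 4 v 0 illustration also assumes no censoring before the last event. If the four events fall in the arm of 29 instead, the log-rank p is 0.034 and the likelihood-ratio p 0.014, with Wald still near 1.

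The competing-risk point is secondary. It applies only to non-fatal types and only if deaths are censored, which is the usual reading but is not stated. It concerns curves read as risks: a Cox hazard ratio with death censored is still a valid cause-specific hazard ratio.

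**What to change.** Keep Cox regression for each event type and replace the Wald statistic. Possible wording: hazard ratios for single event types will be estimated by Firth-penalised Cox regression with profile penalised-likelihood 95% confidence intervals and the matching likelihood-ratio p value; where neither arm has an event, only counts will be given. Ordinary profile-likelihood intervals, with a likelihood-ratio or log-rank p value, would also serve, but they are unbounded on one side when an arm is empty. Choose one method in advance, since 4 v 0 gives p values on both sides of 0.05 depending on the method.

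As a minor addition, show Aalen-Johansen cumulative incidence with death as a competing event for non-fatal components, and keep Kaplan-Meier for all-cause death and the composite.

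The cost is two sentences and slightly more analysis work with standard software options. Intervals for rare components will be very wide, as the Firth upper limit of about 1,174 shows; that is a fair picture of what 60 patients can say.

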#### Shorter term safety outcomes

Numbers of events and numbers (%) of patients with events will be summarised. Relative frequency of event types will be compared using Fisher’s exact tests and ORs and 95% CIs for treatment effects estimated using exact logistic regression.

Changes in quality of life over time will be analysed at each time point using analysis of covariance adjusting for baseline and using repeated measures analysis of postintervention data adjusting for baseline. The prespecified health outcomes will be analysed at each time point using ordinal logistic regression adjusted for baseline.

All serious adverse events will be summarised according to system organ class and preferred term.

## Ethics and dissemination

The research study was reviewed and approved by the National Research Ethics Service (Reference 11-WS-0116).

Potential benefits to participants include avoidance of harmful invasive management and avoidance of longer term stent failure. No additional interventions are proposed nor are procedures withdrawn that would be needed on clinical grounds. While the intention-to-treat in each group is either with non-invasive or invasive management, all treatment options remain available according to patient and physician preference, that is, patients initially randomised to medical therapy may undergo invasive management and vice versa.

*Data management and biostatistics*: For confidentiality, patients shall be assigned an identification code at the time of recruitment.

### Trial management

A *trial management group* including the researchers and Local Principal Investigator on each of the four sites coordinated the study's activities on a day-to-day basis.

The NHS Sponsor monitored the trial. Since the trial was a pilot, there was no Independent Data and Safety Monitoring Committee (IDMC).

*The trial is publically registered*:^27^
http://clinicaltrials.gov/ct2/show/NCT01895751.

*Expected value of results*: Since clinical trials usually excluded patients with prior CABG, clinical guidelines are not evidence-based with respect to this group of patients meaning that clinicians lack knowledge, and a clinical decision in favour of invasive management (as per guidelines) is not well informed. Our project addresses this lack of evidence. If a future substantive trial confirms our overall hypothesis, then routine non-invasive management should be adopted generally, except for the minority with refractory angina who would be selectively referred for invasive angiography. The trial results will help reduce unnecessary and expensive diagnostic investigations (ie, stress tests) and provide clarity for decision-making. The results from a future definitive trial could be rapidly implemented in routine NHS practice. This research proposal will provide essential information to inform the design of the future substantive trial, including whether or not it should be performed and if so, its sample size and primary and secondary outcomes.
